However, the clinical role of telemedicine in patients with optimally controlled BP is unclear because existing RCTs included patients with elevated BP, and telemedicine typically represented more intensive treatments in these RCTs [3–7]. The ideal frequency of telemedicine monitoring in patients with optimal BP control remains unknown [3]. There is also uncertainty whether telemedicine can reduce or replace clinic visits, with limited relevant evidence [3]. Similarly, the cost and safety of telemedicine are under-reported in existing RCTs [3]. Importantly, the role and effectiveness of telemedicine are understudied in Chinese. With the latest meta-analysis on telemedicine and HT only including one Chinese RCT (*n* = 59), ranked as having a high risk of bias [6]. Understanding the factors to enhance the effectiveness and successful implementation of telemedicine systems, such as taking into consideration different cultures, patients’ age and education, and healthcare system organisations, is vital [8].

To examine the feasibility of using a telemedicine system to reduce doctor consultations, we conducted a 6-month pilot RCT (*n* = 49) in 2020 which randomised patients with optimal BP control to a telemedicine arm or a usual care arm [9]. The telemedicine system (called “HealthCap”) used in the pilot RCT was developed by our team. It can record home BP measurements (HBPM), provide automatic feedback on different BP levels, transfer BP data to the case physicians, and confirm optimal BP control on HBPM (details under methods) [9]. For patients randomised to the HealthCap intervention, drugs were prescribed in the clinic without doctor consultation, and the index physician’s consultation was deferred after optimal BP control was confirmed by HealthCap. Our pilot RCT found that (i) patients’ retention was high (98%), (ii) patients’ acceptability was high, which was further confirmed by patients’ interviews (interviewees reported that HealthCap was convenient, time-saving, cost-saving, and educational), (iii) no side effects or hospitalisation was detected in both groups, (iv) similar SBP/DBP control between the two groups at 6-month follow-up (systolic BP: 128.2 versus 126.9 mmHg [telemedicine versus usual care], *p* = 0.41), and (v) clinical visits were reduced in the telemedicine group (0.8 versus 2 consultations, *p* < 0.001) [9]. Our pilot RCT also confirmed the feasibility of using HealthCap in general outpatient clinic (GOPC) settings [9].

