### Outcome measures

#### Primary outcome: daytime ABPM BP at 12 months

ABPM is the reference standard for BP measurements because of its superior reproducibility and predictability of cardiovascular outcomes [13, 14]. Mean daytime SBP will be the primary outcome of the RCT. SBP instead of DBP will be our primary outcome because SBP is more predictive of cardiovascular events than DBP, especially in the elderly [18]. WatchBP O3 (Microlife AG, Switzerland) has been validated by multiple HT societies (www.stridebp.org) and will be used in the current RCT. ABPM will be conducted in accordance with international guidelines (including the use of the non-dominant arm and appropriate cuff size) [19]. BP will be measured every 30 min for ≥24 h, and patients’ sleep diary will define the sleep duration. The readings will be considered valid if there are >70% valid readings overall, >20 valid awake, and >7 valid asleep BP readings in 24-h intervals [19]. Furthermore, erroneous and physiologically impossible BP readings are excluded (i.e. SBP outside the range of 50–240 mmHg and DBP outside the range of 40–140 mmHg) [19].

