### Sample size calculation

According to existing literature, a minimal clinically meaningful difference was set at an SBP difference of 2 mmHg [26]. By further setting type I error at 5% and type II error at 20%, and a standard deviation (SD) of 10 mmHg on ABPM (this is our primary outcome, and we observed this SD in our previous local studies) [27], the required sample size for this non-inferiority RCT will be 309. At the maximum dropout rate of 15%, 364 patients are required.

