### Statistical analysis

The baseline characteristics of the participants in the two arms will be described using means with SD and proportions for continuous and categorical variables, respectively. The effect of the HealthCap telemedicine system on SBP measured by ABPM (our primary outcome) will be examined using analysis of covariance (ANCOVA) with baseline SBP measured by ABPM and the treatment group as the covariate, following the intention-to-treat (ITT) principle, that is, patients will be encouraged to conduct ABPM at 12 months regardless of whether they comply with the assigned intervention. A per-protocol (PP) analysis will be conducted for sensitivity analysis. PP analysis provides some protection for theoretical increases in the risk of type I errors (erroneously concluding non-inferiority). Our modified ITT (mITT) data comprised all patients according to and were included in the random allocation of complete data. We defined the PP population as participants who met the mITT definition but did not receive intervention treatments. Based on a previous meta-analysis, we set the non-inferiority margin for ABPM SBP at 2 mmHg [26]. We accepted the non-inferiority of telemedicine over usual care (in a 0.0125-level test after Bonferroni correction for multiple testing) if the lower bound of the two-sided 95% confidence interval (CI) (equivalent to the upper bound of the one-sided 97.5% CI) was within the non-inferiority margin. Subgroup analysis will be conducted in cases of unbalanced baseline characteristics and for patients with and without indications of a lower BP target (i.e. <130/80 mmHg). Additionally, missing data will be addressed through multiple imputation.

Qualitative data will be analysed by at least 2 investigators using inductive thematic analysis as described by Braun and Clarke [28]. Therefore, digital recordings will be transcribed verbatim. The recordings will be listened to several times, and the transcripts will be read and re-read by at least 2 investigators. After familiarisation, codes and then themes will be generalised. The investigator team will discuss the themes to determine and decide on any over-arching themes. The Consolidated criteria for Reporting Qualitative Research (COREQ) Checklist will be followed throughout the qualitative research part to ensure comprehensiveness and transparency in reporting qualitative findings [29].

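### The non-inferiority rule equates a lower confidence limit with an upper one and fixes neither the direction of the difference nor the sign of the 2 mmHg margin

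*Protocol article*

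**What the plan says.** The primary endpoint is a blood pressure at 12 months: "Mean daytime SBP will be the primary outcome of the RCT". Its analysis is introduced as an effect of the intervention: "The effect of the HealthCap telemedicine system on SBP measured by ABPM (our primary outcome) will be examined using analysis of covariance (ANCOVA"), adjusted for baseline.

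The margin has no sign: "we set the non-inferiority margin for ABPM SBP at 2 mmHg". The success criterion follows in the same section of the Protocol article. It opens "if the lower bound of the two-sided 95% confidence interval (CI) (equivalent to the upper bound of the one-sided 97.5% CI" and then requires that this bound be within the margin. The same sentence sets the test level: "in a 0.0125-level test after Bonferroni correction for multiple testing".

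No section writes out which arm is subtracted from which. The nearest indications are the wording of the ANCOVA sentence, which speaks of the effect of HealthCap, and the pilot result in the Background, "systolic BP: 128.2 versus 126.9 mmHg [telemedicine versus usual care"]. No other section states the deciding bound.

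**The concern.** For systolic pressure, harm from telemedicine appears as a higher mean. If the difference is telemedicine minus usual care, non-inferiority means ruling out an excess of 2 mmHg or more, and only the upper confidence limit can do that. A lower limit below +2 shows only that the data do not prove an excess of 2 mmHg, which is a different and much weaker statement.

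The sentence names the lower limit, equates it with an upper limit, and leaves open what *within* means for an unsigned margin. Two analysts could apply it to the same data and reach opposite conclusions. This sentence decides whether telemedicine is declared able to replace consultations. Under Aims and objectives, the result also decides whether the cost-minimisation analysis is done.

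**Working it through.** **Inputs.** SD 10 mmHg, 309 before dropout and 364 after 15% dropout (Sample size calculation); 1:1 allocation (Trial design); margin 2 mmHg and two-sided 95% CI (Statistical analysis).

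**The plan's own figures.** The dropout step reproduces: 309/0.85 = 363.5, so 364. The 309 reproduces as 2 × (1.645 + 0.842)² × 10²/2² = 309.1, which is a per-arm number at one-sided 5%; the article uses it as the trial total. That is a separate matter. Below, 309 and 364 are taken as totals, as the article does.

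**Distance between the limits.** SE = SD × √(4/N), and half-width h = 1.96 × SE.
- N = 309: SE = 10 × √(4/309) = 1.138; h = 2.23; the limits are 2h = 4.46 mmHg apart.
- N = 364: SE = 1.048; h = 2.05; 2h = 4.11 mmHg.

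The upper limit of a one-sided 97.5% CI is the upper limit of the two-sided 95% CI. The gap to the lower limit is more than twice the margin.

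**Acceptance if D = telemedicine minus usual care and the true excess is d.**
- Rule A, lower limit below +2: P = Φ(1.96 − (d − 2)/SE).
- Rule B, lower limit between -2 and +2: P = rule A minus Φ((−2 + h − d)/SE).
- Rule C, upper limit below +2: P = Φ((2 − h − d)/SE).

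Example with N = 309, d = 3, rule A: Φ(1.96 − 1/1.138) = Φ(1.081) = 86.0%. Example with d = 2, rule B: 97.5% − Φ(−1.556) = 97.5% − 6.0% = 91.5%.

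| True excess (mmHg) | A, N=309 | A, N=364 | B, N=309 | B, N=364 | C, N=309 | C, N=364 |
|---|---|---|---|---|---|---|
| +2 | 97.5% | 97.5% | 91.5% | 94.3% | 2.5% | 2.5% |
| +3 | 86.0% | 84.3% | 85.3% | 84.0% | 0.2% | 0.2% |
| +4 | 58.0% | 52.1% | 58.0% | 52.1% | <0.1% | <0.1% |
| +5 | 24.9% | 18.4% | 24.9% | 18.4% | <0.1% | <0.1% |

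**Sensitivity to the SE.** ANCOVA multiplies the SE by √(1 − r²), where r is the correlation with baseline. The article gives no r. If one assumes r = 0.71, the variance halves and SE = 1.138 × √0.5 = 0.805 at N = 309. Rule A then gives Φ(1.96 − 1/0.805) = 76% at +3 and Φ(1.96 − 2/0.805) = 30% at +4. At +2 it remains Φ(1.96) = 97.5% whatever the SE.

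**Illustration.** Take the pilot's difference, 128.2 − 126.9 = +1.3 mmHg, with SE 1.138. The CI is 1.3 ± 2.23, or -0.93 to 3.53. Rules A and B accept; rule C rejects. Reversing the subtraction gives -3.53 to 0.93, and the rule *lower limit above -2* rejects, in agreement with rule C. The outcome therefore turns on a direction that the article does not state.

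**Level.** A two-sided 95% CI corresponds to one-sided 0.025. A one-sided 0.0125 test needs z = 2.241, so at N = 309 the half-width is 2.55 mmHg instead of 2.23. The Sample size calculation has a third figure, "By further setting type I error at 5% and type II error at 20"%, with sidedness not stated.

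**The case against.** The strongest reply is that the sentence can be read coherently. The lower 95% limit of usual care minus telemedicine is exactly the negative of the upper one-sided 97.5% limit of telemedicine minus usual care. Testing the first against -2 is the same as testing the second against +2. On that reading the rule is sound and the parenthesis is a loosely worded reminder of the equivalence. The sentence also names the safe bound, so the fault may be one of drafting. All of this stands as a possibility, but the article states neither a reversed contrast nor a negative margin, and its own phrasing points the other way.

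A reader might infer that the plan has adopted a rule with 97.5% type I error that would accept clearly inferior care. The documents do not support that. It requires telemedicine minus usual care, which is suggested and not defined. It requires *within* to be one-sided, and it discards the half of the sentence that names an upper bound. Nor would such a rule almost never fail: at a true excess of 4 mmHg it fails 42% of the time with 309 analysed.

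A reader might also infer that the bound will be chosen by people who know the allocation. Investigators, participants and healthcare providers are indeed unblinded, but the Randomisation/blinding section keeps the analysing statisticians blinded.

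An unseen analysis plan is no answer. The point is not that the rule is missing, but that the rule printed here is inconsistent on its face.

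**Conclusion.** The concern holds as a defect in how the primary decision rule is written. Direction, sign and deciding bound are not fixed, and for any single contrast the stated equivalence is false. The rule is wrong on the orientation that the article suggests and undefined otherwise.

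The size is conditional. The acceptance probabilities at +2, +3 and +4 apply only to telemedicine minus usual care. They use a normal approximation and SD 10, with 309 or 364 analysed. The figures at +3 and +4 fall if ANCOVA gains precision. Under rule A the 97.5% at the margin does not depend on the SE; under rule B the figure at the margin does. Under usual care minus telemedicine with a margin of -2, there would be no inflation at all.

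Because this one sentence determines the trial's conclusion, it should be corrected before the 12-month data are analysed.

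**What to change.** Replace the criterion with wording such as: *The effect is the adjusted mean difference, HealthCap minus usual care, in daytime ABPM systolic pressure at 12 months. Non-inferiority is concluded only if the upper confidence limit is below +2 mmHg.*

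In the same edit, state one confidence level and its sidedness. Either the two-sided 95% CI (one-sided 0.025) is kept and the 0.0125 level is removed or explained, or the interval is widened to match 0.0125 and the tests sharing the Bonferroni correction are named. The type I error in the Sample size calculation should then agree.

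The cost is one sentence in the protocol, carried into any analysis plan and through the ethics approvals that the article requires for amendments. No data collection changes, and recruitment stood at 114 of 365 when the article was written. The corrected rule does make the sample size question visible. At a true difference of zero and SD 10 without ANCOVA gain, it succeeds with probability 42% (309 analysed) or 48% (364) at one-sided 0.025, and 31% or 37% at 0.0125. That should be taken up separately and is no reason to leave the rule as it is.

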### Randomisation/blinding

Stratified randomisation with blocks of four or six will be used according to (i) the presence or absence of diseases that increased cardiovascular risk and required a lower BP target (<130/80 mmHg) (including DM, history of cardiovascular diseases, history of chronic kidney disease) and (ii) the number of anti-HT medications (<3 or ≥3) because the number of medications affects medication adherence and the likelihood of maintaining optimal BP control [17]. The randomisation sequence will be generated by an independent statistician, using the statistic programme Random Allocation Software, version 1.1.0, printed out, and sealed in light-opaque envelopes, which will only be opened by the research assistant after a participant’s eligibility is confirmed and the consent form is signed. Due to the nature of the intervention, blinding the investigators, participants, and healthcare providers will be infeasible after randomisation. However, the independent statisticians who will conduct the analysis will remain blinded.

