Physicians will be asked about their experience of (i) introducing the HealthCap system to the patients, (ii) the drug auto-refill process and any relevant difficulties and concerns, (iii) a change in the doctor-patient relationship, (iv) any extra workload due to the use of the HealthCap system, (v) how HealthCap changes their usual practice and any perceived unmet patients’ health needs, and (vi) how likely that they will continue to promote and use the HealthCap system for these patients.

Similarly, patients randomised to use the HealthCap system will be asked about their experience with (i) a more frequent HBPM and self-management, (ii) any observed health changes and difficulties due to the HealthCap system, (iii) any unmet health needs during the last 1 year, (iv) the automatic drug refill process, (v) a change in the doctor-patient relationship, and (vi) how likely that they will continue to use the HealthCap system. The questions may be modified according to the quantitative results or any difficulty using HealthCap detected during the RCT. Data will be collected until saturation is reached.

Baseline data collection: Data on age, sex, marital status, educational level, smoking status (current smoker, ex-smoker, or never smoked), and alcohol use (assessed by the validated Alcohol Use Disorders Identification Test questionnaire) will be collected on recruitment [24]. Furthermore, eHealth literacy will be assessed using the validated Chinese 8-item eHealth literacy scale, which has high internal consistency (Cronbach’s alpha = 0.95) and has been used in Chinese with chronic diseases [25].

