An interim report will be submitted by the principal investigator to the Health and Medical Research Fund, Hong Kong SAR, the funder of the current study only for its review and record (available at https://rfs1.healthbureau.gov.hk/english/funds/funds_hmrf/funds_hmrf_abt/funds_hmrf_abt.html). The report will include updates on the aims and objectives of the research, the timetable of work, and the achievements and major findings of the project to date. It will also detail expenditure and provide comments on the potential for disseminating research findings. Additionally, we will report on the recruitment rate, assess the balance between the two arms of the study, including any demographic imbalances that may be of concern, and report any interim results. Furthermore, we will document any trial-related adverse events and severe adverse events encountered during the study. The principal investigator will closely monitor participant safety during the study period. In the event of an adverse event, the principal investigator will review the case and report to the ethics committee for record and investigation. Although no harm to participants is expected from this study, we have consistently reported all severe adverse events to the ethics committee within 1 to 2 days of becoming aware of them. Should any concerns arise regarding the trial, the ethics committee has the authority to halt the trial at any time. Clinical trial insurance was purchased to cover compensation for participants who are harmed as a consequence of participation in this study. Financial auditing of the current study will be performed by the Chinese University of Hong Kong SAR.

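### Subgroup analyses are triggered by chance baseline imbalance, while the overall estimate stays unadjusted for the factor that triggered them

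*Protocol article*

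**What the plan says.** The Statistical analysis section gives two grounds for subgroup analysis in one sentence. The first is: "Subgroup analysis will be conducted in cases of unbalanced baseline characteristics". It depends on what the baseline table turns out to show. The second, a split by whether a lower BP target is indicated, is fixed in advance and matches one of the two stratification factors.

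Three other statements bear on it:

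- The primary model is "analysis of covariance (ANCOVA) with baseline SBP measured by ABPM and the treatment group as the covariate". No other covariate is stated, and neither stratification factor is in the model.
- Baseline data are summarised only: "The baseline characteristics of the participants in the two arms will be described using means with SD and proportions". The section gives no test or threshold for calling a characteristic unbalanced.
- Under Randomisation/blinding, "Stratified randomisation with blocks of four or six will be used". The strata are the presence of disease requiring a lower BP target and the number of antihypertensive drugs (<3 or ≥3).

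**The concern.** Two different questions are merged. A subgroup analysis asks whether the treatment effect varies with a factor. A baseline imbalance raises the question whether a prognostic factor has shifted the overall contrast between arms. Covariate adjustment answers the second question; splitting the trial does not.

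Under the stated rule, the list of subgroups is settled by chance differences between arms. Readers may be shown subgroup results that nobody had a reason to expect. Meanwhile the overall estimate, on which the trial's conclusion rests, is not adjusted for the factor that prompted the extra analysis. At stake are the credibility of the secondary subgroup results and the lack of a planned sensitivity analysis that would address imbalance directly.

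**Working it through.** The plan gives no figure of its own for this rule, so there is nothing to reproduce. The check has three parts.

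**1. What the rule does to each estimate.** Suppose factor X is unbalanced.

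- Subgroup analysis by X gives one treatment contrast within each level of X. Inside a level the arms no longer differ on X, so each contrast is free of that imbalance.
- The protocol names no step that combines these contrasts. The overall estimate still comes from the ANCOVA on baseline systolic pressure and treatment, and X is not in it.
- Adding X to that model would adjust the overall estimate. No such step is stated.

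**2. How often chance alone could trigger the rule.** The candidate variables are in the Secondary outcomes section.

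- The baseline data paragraph lists six: "Data on age, sex, marital status, educational level, smoking status (current smoker, ex-smoker, or never smoked), and alcohol use". It then adds a seventh: "eHealth literacy will be assessed using the validated Chinese 8-item eHealth literacy scale". So k = 7.
- The paragraph on other physical parameters adds creatinine, fasting glucose, HbA1c, four lipid measures and body mass index, all taken at baseline. That is 8 more, so k = 15.

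Assume, since the protocol does not say, that unbalanced means p<0.05 and that the variables are independent. The chance of at least one trigger under sound randomisation is 1 − 0.95^k:

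- k = 7: 1 − 0.95^7 = 0.30
- k = 15: 1 − 0.95^15 = 0.54

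A different assumed criterion gives similar figures. Take a standardised difference above 0.2 with 364/2 = 182 per arm. Its standard error is √(2/182) = 0.105, so z = 0.2/0.105 = 1.91 and the two-sided probability is 0.056. Then 1 − (1 − 0.056)^k is 0.33 for k = 7 and 0.58 for k = 15. Positive correlation, as expected between fasting glucose and HbA1c or among the lipids, lowers all four figures.

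**3. What adjustment would change.** This is an illustration with assumed inputs: 182 per arm, a binary factor with 30% prevalence, a 5 mmHg effect on systolic pressure, residual SD 10 mmHg and no treatment effect. Only trials in which the arms differ on the factor by more than 9.4 percentage points are kept. That cut-off is about 1.96 × √(2 × 0.3 × 0.7/182) = 0.094, the two-sided 5% point.

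- At the cut-off, the unadjusted difference is shifted by 5 × 0.094 = 0.47 mmHg.
- Averaged over 4,000 simulated trials beyond the cut-off, the shift is about 0.58 mmHg.
- With the factor as a covariate, it is about 0.01 mmHg, which is simulation noise.
- Subgroup analysis leaves the overall estimate where it was.

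The 0.58 mmHg depends on the assumed 5 mmHg effect and on selecting the unbalanced trials. It shows which tool acts on the overall estimate. It is not a forecast for this trial.

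**The case against.** Much can be said for the plan.

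- *The primary test is sound without further adjustment.* Baseline ABPM systolic pressure, probably the strongest predictor of the outcome, is already in the model. Lower-target disease and number of drugs are balanced by stratification. The confidence interval of a randomised comparison already allows for residual chance imbalance. This stands, and it limits the point to secondary and sensitivity analyses.
- *Stratifying by the factor does remove its imbalance within each level.* This also stands. It would be wrong to say that the rule corrects nothing; what it leaves uncorrected is the overall estimate.
- *The trigger uses baseline data, not outcomes, and the analysing statisticians are blinded.* True. This is not selection of favourable results.
- *The threshold, the candidate list and the interaction tests may be in an unseen SAP.* They may, and their absence here is not the complaint. But the protocol itself states the trigger, and a defined threshold would still leave subgroup choice to chance imbalance.

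A reader might infer two stronger points that the document does not support.

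- *That each triggered subgroup will be judged against the 2 mmHg margin and is too small for it.* The margin and acceptance rule are stated for telemedicine against usual care; no subgroup claim is announced. With 309 evaluable and SD 10 mmHg, a half-size subgroup has a 95% half-width of 1.96 × 10 × √(2/77.25) = 3.15 mmHg. That ignores the ANCOVA gain: at assumed baseline correlations of 0.5 and 0.7 it becomes 3.15 × √0.75 = 2.73 and 3.15 × √0.51 = 2.25 mmHg. On the same raw-SD basis the whole trial has 1.96 × 10 × √(2/154.5) = 2.23 mmHg. The width reflects the sample size, not this rule.
- *That the interim report feeds the trigger.* The Monitoring and adverse event management section says that report will "assess the balance between the two arms of the study, including any demographic imbalances that may be of concern". It goes to the funder for review and record, and no subgroup analysis is tied to it.

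**Conclusion.** The point holds in limited form. The protocol fixes a rule that selects subgroups by chance baseline imbalance, which says nothing about effect modification, and it states no adjustment of the overall estimate for the factor concerned. The primary non-inferiority test is not invalidated.

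The 30% to 54% trigger range is illustrative. It rests on an assumed p<0.05 criterion, independent variables and 7 to 15 candidates, and true correlation would make it lower. The conclusion does not depend on that range: the rule is the wrong tool for imbalance however often it fires. The lower-BP-target subgroup in the same sentence is pre-specified and is not criticised.

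**What to change.** - Delete baseline imbalance as a ground for subgroup analysis.
- Keep the lower-BP-target subgroup. Estimate it by a treatment-by-stratum interaction in a model separate from the primary ANCOVA, so that the primary treatment coefficient keeps its meaning. Report the stratum estimates and the interaction with confidence intervals, with no separate non-inferiority claim.
- Add one covariate-adjusted sensitivity ANCOVA, fixed before unblinding. It should contain treatment, baseline ABPM systolic pressure, the two stratification factors and a short pre-specified list of prognostic baseline variables already collected, for example age and sex.

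A fixed list will not cover an imbalance in a variable left off it, so the list should be chosen on prognostic grounds. The cost is a change of wording and one extra model, with no new data. The Trial status section reports 114 of 365 participants recruited, so the change can still be made while recruitment is under way.
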